# STATISTICAL CONSIDERATIONS

## Rationale for the sample size

Based on the results of the Hvidore study (Holl RW Eur J Pediatr 2003), we assume that the HbA1c level will follow a normal distribution, with a standard deviation of 1.6. The sample size necessary was calculated to evidence a difference in HbA1c level between the 2 “standard management” and “text messaging” groups of at least 1% after a 6-month follow-up period. Taking into account a type I error of 5% and 80% power, 41 subjects per group, i.e. 82 subjects in total, will need to be included and randomised.

To take into account a potential rate of refusal to take part in the “text messaging” arm, of approximately 10%, the sample size necessary was increased by 20%, i.e. 50 subjects per group, 100 subjects in total (Zelen, Stat med 1990).

Children who withdraw their consent, after being randomised to the “text messaging” arm will be followed up under the same conditions as those in the “standard management” group.

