### Procedures for limiting missing data

No or very few patients will be “lost to follow-up”, in view of their age and their usual obligations in terms of medical follow-up. The number of missing data should be very low.

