## WITHDRAWAL FROM THE TRIAL AND PREMATURE WITHDRAWAL

The participants will leave the study after the 6-month follow-up period.

The patient, or person with legal authority, may withdraw their participation in the study at any time, without their decision compromising their continued treatment, quality of care or relationship with their doctor in any way.

Any patients erroneously included and not fulfilling the inclusion and exclusion criteria will be prematurely withdrawn from the trial. Other deviations from the protocol will not be considered as study withdrawals.

The investigator should document the reasons for premature withdrawal as thoroughly as possible. Study withdrawals should notably be related to the following reasons:

- Refusal by the subject or his/her parents to continue taking part in the trial
- Patient included erroneously
- Patient lost to follow-up

If a participant does not attend the follow-up visits, the investigator responsible for the patient’s care should contact the patient to determine his/her condition at the time of withdrawal from the study. If it is impossible to contact the patient, s/he will be considered lost to follow-up at the date of the last visit.

Patients withdrawn from the trial cannot be re-included in the study. Their inclusion number will not be re-used.

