## Description of planned statistical methods, including the planned interim analysis schedule

The statistical analysis will be carried out using SAS software, under the supervision of [name] (Paris Centre CRU - Cochin-Necker). The statistical analysis will be carried out at the end of data collection, data entry and data consistency checks.

A descriptive analysis of the characteristics of the children included in each group will be performed first of all. Quantitative data are expressed as the mean ± standard deviation or median and range, and as the sample size and percentage for qualitative data.

The primary endpoint and secondary endpoints will be analysed on an intention-to-treat basis, i.e. all randomised patients will be analysed in their randomisation arm, irrespective of the intervention received. All tests used will be two-sided, with a 5% significance level.

*Main analysis*

The HbA1c level after the 6-month follow-up period will be compared between the “text messaging” and control groups using Student’s *t*-test.

*Secondary analyses*

The HbA1c level after the 3-month follow-up period will be compared between the “text messaging” and control groups using Student’s *t*-test.

For all secondary endpoints, satisfaction and compliance, two means will be compared using Student’s *t*-test or a Wilcoxon test if necessary. The percentages will be compared using the Pearson Chi-2 test or Fisher’s exact method, if necessary.

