Appendix 4: 3 MONTH FOLLOW-UP DATA COLLECTION FORM

Impact of Mobile Phone Short Text Messages on the Glycaemic Control of Adolescents With Poorly Controlled Type 1 Diabetes.

Appointment date: …/.../... (dd/mm/yyyy)

1) Study data: to be completed by the coordinator

Patient code: |__|__|__| |__|__|__| |__| |__|

2) HbA1c level

Sampling date for second HbA1c level: …/.../... (dd/mm/yyyy)

Result: ….... %

3) Adverse event to be notified, comments:

…....................................................................................................................................................................

…....................................................................................................................................................................

4) Collection of the capillary blood glucose diary: yes no

Percentage of insulin injections recorded _ _%

5) Distribution and collection of the quality of life questionnaire: yes no

6) Distribution of the second capillary blood glucose diary: yes no

7) If the patient has been randomised to the text messaging arm:

Did s/he send a “STOP” text message yes no

If “yes”, date on which this text message was sent: …/.../... (dd/mm/yyyy)

If this is the case, in a single sentence, indicate the main reason given by the adolescent: ……………………………………………………………………….

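### The increase from 41 to 50 per group is right for about 10% refusal but is wholly used by it; the sample size leaves nothing for missing M6 HbA1c or for further stopping of messages

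*Protocol*

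**What the plan says.** Section 12.1 takes its spread from an international survey of adolescents with type 1 diabetes: "we assume that the HbA1c level will follow a normal distribution, with a standard deviation of 1.6". The target is a difference of at least 1 HbA1c percentage point at 6 months. The result is: "Taking into account a type I error of 5% and 80% power, 41 subjects per group, i.e. 82 subjects in total".

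The section then gives a single reason for enlarging the trial, a refusal rate of about 10% in the text messaging arm, and concludes that "the sample size necessary was increased by 20%, i.e. 50 subjects per group, 100 subjects in total". Its last paragraph adds that children who withdraw consent after allocation to text messaging are followed up like the controls.

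Section 12.2 plans an unadjusted Student's t-test on HbA1c at 6 months, by intention to treat, and says "All tests used will be two-sided, with a 5% significance level".

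Three other places bear on the number of usable values and on the size of the effect:

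- Section 4.4.3 expects no or very few losses, because of the patients' age and usual follow-up, and says "The number of missing data should be very low".
- Section 5.4 lists reasons for withdrawal, among them refusal to continue, erroneous inclusion and "Patient lost to follow-up".
- The M3 and M6 forms (Appendices 4 and 5) ask whether a text-arm patient sent a STOP message and on what date, and tell the clinician to "in a single sentence, indicate the main reason given by the adolescent".

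No rate is given for loss, erroneous inclusion or stopping.

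**The concern.** The protocol claims 80% power. A sample size increase of a fifth looks like a general reserve, but the text ties all of it to one event, refusal of the messages. Two other events act on power in different ways. A missing M6 HbA1c reduces the number analysed. A patient who stops the messages stays in the text arm under intention to treat and shrinks the difference. If refusal alone uses the whole increase, the 80% rests on complete M6 data and on no stopping beyond the 10%, and section 12.1 does not say so.

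What is at stake is the reading of a null result. A non-significant test would be taken as evidence against a 1-point effect with somewhat more assurance than the design provides.

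**Working it through.** **Inputs from the protocol.** SD 1.6, difference 1.0, type I error 5%, power 80%, refusal about 10%, 50 per group (12.1); two-sided test, intention to treat, Student's t-test (12.2).

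**Inputs that are assumptions.** M6 loss of 5% or 10%; further stopping of 5% or 10%; the share of benefit that a stopper keeps; the baseline-M6 correlation. The protocol gives none of these.

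**1. The protocol's own figure.** n = 2 × (1.96 + 0.8416)² × 1.6² / 1.0² = 40.2, so 41 per group. This reproduces 12.1. The noncentral t gives 79.8% at 41 and would need 42.

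**2. The allowance for refusal.** Refusers are analysed in the text arm, so the expected difference is 0.9 × 1.0 = 0.9. Then n = 40.19 / 0.9² = 40.19 / 0.81 = 49.6, so 50 per group, which is the stated number. The other route agrees: 41 × 1.20 = 49.2, so 50.

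**3. What is left.** Power at 50 per group:

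| Situation | Normal formula | Noncentral t |
|---|---|---|
| No refusal (difference 1.0) | 87.8% | 87.2% |
| 10% refusal (difference 0.9) | 80.3% | 79.5% |

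Refusal takes power from about 88% to about 80%. No reserve remains.

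**4. Missing M6 values.** With 10% refusal and loss m in both arms, the number analysed is 50 × (1 − m) per group:

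| Assumed M6 loss | Analysed per group | Normal formula | Noncentral t |
|---|---|---|---|
| 0% | 50 | 80.3% | 79.5% |
| 5% | 47.5 | 78.3% | 77.4% |
| 10% | 45 | 76.1% | 75.1% |

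**5. Stopping beyond the 10%.** If a further fraction f of text-arm patients stops and keeps a share k of the benefit, the difference is 0.9 × (1 − f(1 − k)). Power by noncentral t:

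| Further stopping | M6 loss | Stoppers keep half | Stoppers keep nothing |
|---|---|---|---|
| 5% | 0% | 77.5% | 75.4% |
| 5% | 5% | 75.3% | 73.1% |
| 10% | 10% | 70.8% | 66.1% |

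**6. Adjustment for baseline.** With a baseline-M6 correlation r, the residual SD is 1.6 × √(1 − r²). With 45 analysed per group and difference 0.9, power by noncentral t is:

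| Assumed r | Residual SD | Power at 10% loss |
|---|---|---|
| 0 (unadjusted) | 1.60 | 75.1% |
| 0.3 | 1.53 | 79% |
| 0.4 | 1.47 | 82% |
| 0.5 | 1.39 | 86% |

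Power passes 80% at a correlation of roughly 0.35. This table assumes no stopping beyond the 10%.

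**The case against.** The strongest reply is that the sample size is correct and its assumptions are mostly open. Much of that stands.

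- **The step itself.** A reader might infer that 20% is the wrong inflation, because 1/0.81 is 1.235. The document does not support this. The actual step from 41 to 50 is 22%, the unrounded requirement is 49.6, and 50 meets it. The 79.5% by noncentral t mainly reflects a different formula, under which 41 per group is already at 79.8%.
- **Contradiction.** A reader might infer that the withdrawal rules and the STOP fields contradict section 4.4.3. They do not. They provide for events without giving a rate, and a rule for handling losses is compatible with expecting few.
- **Grounds for good retention.** Section 6.1 requires patients able to be followed for 6 months, HbA1c is measured quarterly as part of the care both arms receive, visits are with the including doctor, and section 5.4 has non-attenders contacted. Selection on HbA1c of 8.5% or more is not selection on attendance. At an assumed 5% loss, power falls by only about 2 points.
- **What the 10% covers.** The paragraph after it, on children who withdraw consent after allocation, leaves room to read the 10% as including some later stopping. Those children also keep their M6 value.
- **Erroneous inclusions.** Section 12.2 analyses all randomised patients, so treating these as lost data would be an assumption.

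What the reply does not meet is that section 12.1 gives only one reason for the increase, that this reason uses all of it, and that section 4.4.3, despite its heading on procedures, offers a prediction without a figure.

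**Conclusion.** The point holds as a limited one. Fifty per group is the right number for about 10% refusal under intention to treat, and it is fully spent on that. The stated 80% therefore assumes complete M6 HbA1c and no stopping beyond the 10%.

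The shortfall is modest under mild assumptions: power of about 77-78% with 5% loss and 75-76% with 10%, the ranges spanning the two formulas. It grows if more patients stop, to 70.8% by noncentral t with 10% further stopping, half the benefit kept and 10% loss. That last figure stacks three assumptions and should be read as a sensitivity case, not a forecast. All loss and stopping rates here are assumed. If the 10% already includes later stopping, only the missing-data part remains.

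Nor should a reader infer that baseline adjustment is sure to restore 80%. That depends on a correlation the protocol does not report, and inclusion only at 8.5% or above may lower it by narrowing the baseline range.

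**What to change.** 1. **Section 12.2.** Replace the unadjusted t-test on M6 HbA1c with a comparison of the two arms adjusted for baseline HbA1c (ANCOVA), keeping intention to treat and the two-sided 5% level. Baseline HbA1c is already measured at inclusion, so no data or patients are added. The cost is a change to the main analysis, to be made before outcome data are examined. Any gain depends on the correlation, as shown above; with no correlation, the loss of one degree of freedom is negligible.
2. **Section 12.1.** State that the 80% assumes 10% refusal in total and complete M6 HbA1c. Show the power at 5% and 10% missing. Say whether the 10% includes patients who stop the messages later. This costs only wording and a slightly less favourable stated power.

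The step from 41 to 50 per group needs no correction.

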## Description of planned statistical methods, including the planned interim analysis schedule

The statistical analysis will be carried out using SAS software, under the supervision of [name] (Paris Centre CRU - Cochin-Necker). The statistical analysis will be carried out at the end of data collection, data entry and data consistency checks.

A descriptive analysis of the characteristics of the children included in each group will be performed first of all. Quantitative data are expressed as the mean ± standard deviation or median and range, and as the sample size and percentage for qualitative data.

The primary endpoint and secondary endpoints will be analysed on an intention-to-treat basis, i.e. all randomised patients will be analysed in their randomisation arm, irrespective of the intervention received. All tests used will be two-sided, with a 5% significance level.

*Main analysis*

The HbA1c level after the 6-month follow-up period will be compared between the “text messaging” and control groups using Student’s *t*-test.

*Secondary analyses*

The HbA1c level after the 3-month follow-up period will be compared between the “text messaging” and control groups using Student’s *t*-test.

For all secondary endpoints, satisfaction and compliance, two means will be compared using Student’s *t*-test or a Wilcoxon test if necessary. The percentages will be compared using the Pearson Chi-2 test or Fisher’s exact method, if necessary.

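### The main analysis is an unadjusted t-test on month-6 HbA1c and leaves the baseline and month-3 HbA1c unused, at an avoidable cost in precision

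*Protocol*

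**What the plan says.** Section 12.2 of the protocol (planned statistical methods) fixes the main analysis: "The HbA1c level after the 6-month follow-up period will be compared between the" two arms by Student's t-test. No covariate is named. Month-3 HbA1c has its own separate t-test among the secondary analyses. The same section sets the population as intention to treat ("all randomised patients will be analysed in their randomisation arm, irrespective of the intervention received") and the error rate: "All tests used will be two-sided, with a 5% significance level".

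HbA1c is measured at inclusion, month 3 and month 6 (section 5.1 and the time-line table that follows section 5.3). A value of at least 8.5% at inclusion is an entry criterion (section 6.1).

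Section 12.1 sizes the trial for a difference "of at least 1% after a 6-month follow-up period", "with a standard deviation of 1.6": "Taking into account a type I error of 5% and 80% power, 41 subjects per group, i.e. 82 subjects in total". It then raises this by 20% to 50 per group and attributes the increase to an expected refusal of about 10% in the text-messaging arm.

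On missing values, section 4.4.3 expects that "The number of missing data should be very low" and gives no rate. Section 5.4 allows for withdrawal, erroneous inclusion and loss to follow-up; of a patient who cannot be reached it says "s/he will be considered lost to follow-up at the date of the last visit".

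**The concern.** Baseline HbA1c usually predicts later HbA1c in the same patient. A comparison of month-6 levels that ignores it carries between-patient variation that could be removed at no cost. This holds for every patient in the trial, however complete the follow-up.

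The price matters because the sample size leaves nothing over. The whole inflation is assigned to refusal of the messages, so the trial sits at about its target power before any month-6 value goes missing. Where a value is missing, a two-sample test on month 6 has no use for that patient's baseline or month-3 result, although both may be on file. A trial that could be comfortably powered is left at or slightly below 80%, with a wider confidence interval than its own data allow.

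**Working it through.** **Inputs from the protocol.** Difference 1 HbA1c point, SD 1.6, 80% power, 41 then 50 per arm, refusal about 10% (section 12.1); two-sided 5% (section 12.2).

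**Assumptions, not in the protocol.** Correlation r between baseline and month-6 HbA1c, taken as 0.3 to 0.7; proportion of month-6 values missing, taken as 0 to 20%. The SD is kept at 1.6 after dilution by refusal.

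**1. The plan's own figure.** n per arm = 2 × (1.960 + 0.842)² × 1.6² / 1² = 40.2, rounded up to 41. This reproduces the protocol.

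**2. What the inflation pays for.** 41 × 1.2 = 49.2, taken to 50. With 10% of the text arm refusing and analysed as randomised, the expected difference is 0.9 × 1 = 0.9, which needs 41 / 0.9² = 50.6 per arm. The inflation therefore covers refusal and nothing else.

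**3. Power of the planned t-test (noncentral t).** At 50 per arm the standard error is 1.6 × √(2/50) = 0.32, and 0.9 / 0.32 = 2.81 on 98 degrees of freedom gives 79.5%. If patients without a month-6 value are excluded, power is 77.4% with 5% missing, 75.1% with 10% (45 per arm) and 70.0% with 20%.

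**4. Power after baseline adjustment.** Residual SD = 1.6 × √(1 − r²), difference 0.9:

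| r | Residual SD | Power, 50 per arm | Power, 45 per arm (10% missing) |
|---|---|---|---|
| t-test, no adjustment | 1.60 | 79.5% | 75.1% |
| 0.3 | 1.53 | 83.1% | 79.0% |
| 0.5 | 1.39 | 89.5% | 86.2% |
| 0.6 | 1.28 | 93.6% | 91.0% |
| 0.7 | 1.14 | 97.4% | 95.9% |

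The last column still excludes patients without a month-6 value. A repeated-measures model would also draw on their earlier values.

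**5. Bias, if patients without month 6 were excluded.** Large-sample simulation with SD 1.6, correlation 0.6 between visits, true month-6 difference −0.90, and odds of a missing month-6 value rising e-fold per SD of month-3 HbA1c:

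| Missing, control | Missing, text arm | Estimated difference |
|---|---|---|
| 5% | 15% | −0.98 |
| 15% | 5% | −0.82 |
| 10% | 10% | −0.90 |
| 1% | 3% | −0.92 |

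A shift of 0.08 is a quarter of the standard error of 0.32. It appears only with a threefold difference in loss at rates well above what section 4.4.3 expects.

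**The case against.** The best defence is that nothing here is wrong. An unadjusted t-test on the month-6 level is unbiased under randomisation, and it matches the basis of the sample size, which reproduces. The gain from adjustment depends on a correlation that the protocol does not give, and restricting entry to HbA1c of at least 8.5% narrows the baseline range and may lower that correlation. All of this stands. It makes the point one of efficiency, not of error. It does not remove the gain: even at r = 0.3, power rises by 3 to 4 percentage points at no cost in data.

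Three stronger readings are tempting, and the protocol does not support them.

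- *The main test contradicts the intention-to-treat definition.* Read in context, that sentence governs allocation: patients stay in their randomised arm whatever they received. That is the chief risk in a Zelen design, and a t-test by randomised arm respects it.
- *The protocol prescribes a complete-case analysis.* It does not say so. It states no rule for a missing month-6 value, and such a rule may properly sit in a statistical analysis plan that is not at hand. The power and bias figures under exclusion are illustrations.
- *Objecting to the messages, or sending STOP, causes greater loss in the text arm.* The flow chart and sections 5.2 and 12.1 keep refusers in the same follow-up as controls. The STOP question is on the month-3 and month-6 visit forms, beside the HbA1c result. Full withdrawal is open to both arms.

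**Conclusion.** The point holds as an improvement to a valid analysis. Section 12.2 fixes a main test that uses neither the baseline nor the month-3 HbA1c, in a design whose inflation is already spent on refusal. The firm figure is t-test power of 79.5% at 50 per arm under the protocol's own SD and refusal rate. The gain, to about 83%, 90% or 94%, rests on assumed correlations of 0.3, 0.5 or 0.6. The fall to 75%, and the adjusted counterparts of 79%, 86% and 91%, rest in addition on an assumed 10% of month-6 values missing with those patients excluded.

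Bias from differential missingness is possible but not established. It would be small if missing data are as rare as section 4.4.3 expects. The sample size calculation is not in question.

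**What to change.** In section 12.2, make the primary result the between-arm difference in month-6 HbA1c, by randomised arm, adjusted for baseline HbA1c and reported with its 95% CI.

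The preferred form is a likelihood-based repeated-measures model of HbA1c at baseline, month 3 and month 6, with arm-by-visit means, a common baseline mean and an unstructured covariance. Patients without a month-6 value then still contribute their earlier values, and the same model gives the month-3 comparison. A model of month 6 alone with baseline as covariate would secure most of the precision but would not bring those patients back. Keep the t-test as a sensitivity analysis.

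The cost is a reworded section and slightly more analysis work. No new data, visits or patients are needed.

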In the United States, Hanauer DA. initiated a scheme known as CARDS (computerized automated reminder diabetes system) in 2009. Patients were randomised to two groups: they received an automated reminder to monitor their capillary blood glucose, either by text message (n=22) or by email (n=18). Patients could then enter their capillary blood glucose results and schedule the next reminders. Patients randomised to the text messaging arm recorded more capillary blood glucose results and scheduled more reminders at 1 month. This difference became less marked at 3 months. This population nonetheless found this intervention acceptable.

Joshua S. Borus and Lori Laffel [29] suggest that interventions requiring additional contribution by adolescents can prove to be ineffective due to having an even greater impact on adolescents’ daily lives.

In Scotland, “The Sweet Talk Trial” was conducted in 2010 over a 12-month period, and randomised 64 adolescents and young adults to three groups: standard treatment, standard treatment with “Sweet Talk”, together with intensive insulin therapy and “Sweet Talk”. Patients randomised to the “Sweet Talk” arm also received individual daily text messages as well as text messages referring to their general therapeutic regimen. Although text messaging did not in itself cause a reduction in HbA1c levels, it is nonetheless associated with an increase in self-efficacy and superior compliance reported by patients.

Benhamou published “The Pumpnet Study” [8] in 2007, in France. 15 patients with insulin pumps received weekly medical advice by text messaging over a 12-month period. The author observed an improvement in quality of life (DQOL) and a non-significant reduction in HbA1c level (-0.25+/-0.94%, *p* <0.10) at 12 months.

Lastly, a study conducted in Saudi Arabia, published in March 2014 [12], showed promising results. It was conducted over a 6-month period in 200 children and adolescents with type 1 diabetes. The patients received different types of text messaging support (information messages, interactive messages and video messages). The authors evidenced a significant reduction in fasting blood glucose (from 150 mg/L to 133 mg/L, *p* < 0.001), post-prandial blood glucose, HbA1c level and onset of hypoglycaemia in these patients in comparison with the same parameters prior to the study. This study did not, however, have a control group.

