## ASSESSMENT SCHEDULE FOR THE DIFFERENT GROUPS

The principal endpoint will be assessed at the inclusion visit and during the follow-up visits at 3 and 6 months. The secondary endpoints will be assessed at the follow-up visits at 3 and 6 months.

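### The primary analysis of 6-month HbA1c does not adjust for the baseline HbA1c measured in every patient; the test is valid, but precision available at no cost is left unused

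*Protocol*

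**What the plan says.** Protocol section 12.2 (Main analysis) states: "The HbA1c level after the 6-month follow-up period will be compared between the “text messaging” and control groups using Student’s" t-test. The 3-month comparison uses the same test. The analysis is by intention to treat, and "All tests used will be two-sided, with a 5% significance level". The section names no covariate, change score or adjusted analysis; baseline characteristics are only described by group.

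Baseline HbA1c is available for everyone. Section 5.1 says: "The principal endpoint will be assessed at the inclusion visit and during the follow-up visits at 3 and 6 months". The inclusion form (Appendix 3) has a field for it, and section 6.1 makes a value of at least 8.5% a condition of entry. Section 4.3 describes randomisation in blocks of varying size and states no stratification.

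Section 12.1 sizes the trial for an unadjusted comparison of levels, "with a standard deviation of 1.6" and a difference "of at least 1% after a 6-month follow-up period". It gives: "Taking into account a type I error of 5% and 80% power, 41 subjects per group, i.e. 82 subjects in total". For about 10% refusal in the text-messaging arm, "the sample size necessary was increased by 20%, i.e. 50 subjects per group, 100 subjects in total".

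**The concern.** A patient's starting HbA1c is likely to predict the 6-month value. As far as the protocol states, it is handled neither by the randomisation nor by the primary analysis. Two things follow. The standard error of the treatment difference includes between-patient variation that a measured covariate could explain. And any chance difference in baseline HbA1c between the arms passes into the estimate in proportion to the baseline-to-6-month slope.

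The protocol itself names the primary test, so this is not a detail left open for a statistical analysis plan. The choice is also best settled before the data are seen: adjusting only after an imbalance has appeared would be a data-driven change to the primary analysis.

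**Working it through.** **Inputs from the protocol.** SD 1.6, difference 1 point, two-sided 5%, 80% power, 41 per group before inflation, 50 after, refusal about 10% (sections 12.1 and 12.2).

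**Assumptions.** The correlation r between baseline and 6-month HbA1c is not in the protocol, so it is shown as a range. Refusers are taken to get no benefit, so the intention-to-treat effect is 1 × 0.9 = 0.9.

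**1. The protocol's own figure.** n = 2 × (1.960 + 0.842)² × 1.6² / 1² = 40.2, rounded up to 41 per group. The stated size reproduces. For the inflation, 41 × 1.2 = 49.2, and allowing for dilution 41 / 0.9² = 50.6; the planned 50 agrees closely with both.

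**2. Power of the planned t-test at 50 per group (noncentral t).** About 87% for a difference of 1.0 and 79.5% for 0.9.

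**3. Power with baseline adjustment.** The residual SD is 1.6 × √(1 − r²). With an effect of 0.9 and 50 per group:

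| r | Residual SD | Power |
|---|---|---|
| 0 (t-test) | 1.60 | 79.5% |
| 0.1 | 1.59 | 80% |
| 0.2 | 1.57 | 81% |
| 0.3 | 1.53 | 83% |
| 0.4 | 1.47 | 86% |
| 0.5 | 1.39 | 89.5% |
| 0.6 | 1.28 | 94% |

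**4. If selection also narrows the 6-month spread.** The table holds the SD at 1.6, but entry at 8.5% or more may reduce it. As an illustration, assume an unselected mean of 8% (the figure in section 1.1 for French adolescents), SD 1.6 at both times, bivariate normality and unselected r of 0.5 to 0.7.

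- The cut-off lies (8.5 − 8)/1.6 = 0.3125 SD above the mean. Truncation there leaves a fraction 0.301 of the baseline variance.
- The 6-month SD among entrants is 1.6 × √(1 − r² + 0.301r²): 1.45 at r = 0.5 and 1.30 at r = 0.7.
- The residual SD after adjustment is still 1.6 × √(1 − r²): 1.39 and 1.14.
- With an effect of 0.9 and 50 per group, the t-test has 87% to 93% power and ANCOVA 90% to 97%, a gain of about 3 to 4 points.

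**5. Chance imbalance.** A baseline difference of one standard error shifts the unadjusted estimate by r × 1.6 × √(2/50) = 0.32r. That is 0.10 points at r = 0.3 and 0.16 at r = 0.5, against a target effect of 1.0 (0.9 after refusal).

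**The case against.** The strongest reply is that nothing here is wrong. A t-test on a randomised comparison controls type I error and is unbiased over randomisation, and its standard error already allows for chance baseline imbalance. The sample size uses the SD of the raw level for exactly this test, so design and analysis agree. All of that stands, and it sets the weight of the point.

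Three stronger readings are tempting, and the protocol does not support them.

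- **That power is marginal and adjustment is needed to rescue it.** The 79.5% is essentially the planned 80%, delivered after the refusal that section 12.1 anticipates; without dilution it is about 87%. A further loss from missing 6-month values would be the reader's own scenario, since section 4.4.3 expects very few.
- **That r is known to be high.** A reader might take the pump study in section 1.1, "a non-significant reduction in HbA1c level (-0.25+/-0.94"%, as giving the SD of change and derive a correlation of 1 − 0.94²/(2 × 1.6²) = 0.83. The protocol never says that 0.94 is an SD. Read as one, with 15 patients, t = 0.25/(0.94/√15) = 1.03 and p = 0.32, which does not match the printed p < 0.10. That study also followed a small group of pump users for 12 months. It cannot fix r here, even as an upper bound.
- **That the gain is certainly large.** Selection at 8.5% or more narrows the baseline range and may lower r. At r = 0.1 to 0.2 the gain is only about 0.4 to 1.6 points of power.

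What remains is that the protocol specifies the less efficient of two valid analyses, although the data for the better one are already collected.

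**Conclusion.** The point holds as a recommendation to improve precision, not as a finding of error, bias or inadequate size. That the primary and 3-month tests are unadjusted is certain from section 12.2; the size of the benefit is not.

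With SD 1.6, an effect of 0.9 and 50 per arm, adjustment moves power from 79.5% to between about 80% (r = 0.1) and 94% (r = 0.6). If selection also shrinks the 6-month SD, the t-test is already at 87% to 93% and the gain is about 3 to 4 points. Adjustment also takes out the part of any chance baseline difference that carries through linearly to 6 months. These figures rest on the assumed r, on refusers having no effect and, for the selection case, on the normal model stated there.

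**What to change.** In section 12.2, make the primary analysis an ANCOVA of 6-month HbA1c on randomised arm with baseline HbA1c as covariate, by intention to treat, and report the adjusted mean difference with its 95% confidence interval. Use the same model for 3-month HbA1c. Keep the unadjusted t-test as a sensitivity analysis.

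The cost is a short change of text and one degree of freedom. No extra patients, visits or measurements are needed, and the sample size can stay at 50 per group.
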